## Abstract

**Background:**

Stroke is the main disease that causes the burden of neurological disease, leading to upper limb dysfunction and affecting their self-care abilities. Robot-assisted rehabilitation therapy has been gradually used in the rehabilitation of upper limb function after stroke. However, it would be beneficial to explore auxiliary interventions such as reminiscent music therapy, a combination of music and reminiscent, to relieve negative emotions and post-stroke fatigue and improve rehabilitation outcomes. This protocol aims to evaluate the effectiveness of reminiscent music therapy combined with robot-assisted rehabilitation in older stroke patients.

**Methods:**

This trial is a single-blind, three-arm randomized controlled trial. Older stroke patients with upper limb dysfunction will be recruited. Participants will be randomly assigned to receive usual rehabilitation treatment and care, usual rehabilitation treatment and care plus robot-assisted rehabilitation and reminiscent music therapy, or usual rehabilitation treatment and care plus robot-assisted rehabilitation. Robot-assisted rehabilitation will be conducted by rehabilitation doctors five times per week for 3 weeks. In experimental group 1, a reminiscent song list will be played for patients. The primary outcome is activities of daily living. All outcomes will be evaluated at baseline and in the week immediately post-intervention.

**Discussion:**

We are conducting the first randomized controlled trial on the effects of reminiscent music therapy combined with robot-assisted rehabilitation in older stroke patients. It is expected that this study, if proven effective in improving the activities of daily living in older stroke patients with upper limb dysfunction, will provide evidence-based rehabilitation strategies for medical staff.

**Clinical Trial Registration**: ChiCTR2200063738.

## Introduction

1

Stroke is the leading cause of death and disability in the world (1), and it is also the main disease that causes the burden of neurological disease in old people (2). Under the severe trend of population aging, the incidence rate of stroke increases exponentially with advancing years (3). Of the stroke patients in China, 50.81% are older people aged 60 years or older (4). Stroke is characterized by a high rate of disability, and most stroke patients will experience long-term neurological damage. Persistent upper limb disability occurs in up to 80% of stroke patients (5), which leads to the decline of self-care ability and the need to receive long-term rehabilitation training.

With the development of artificial intelligence technology, traditional medical equipment is constantly developing toward intelligence. Attracting attention in clinical practice, robot-assisted rehabilitation therapy has been gradually used in the rehabilitation of upper limb function after stroke. Some studies have suggested that, compared with traditional rehabilitation treatment, robot-assisted rehabilitation could significantly improve muscle coordination, upper limb function, and social participation in stroke patients (6–10). However, the care burden and economic pressure of patients will be aggravated when suffering from stroke, leading to negative emotions in patients, forming a negative coping style, and inducing post-stroke fatigue with an incidence of 25–85% (11–13). Post-stroke fatigue can affect the subjective feelings of older people’s independent activities and lead to exercise fatigue (14), contributing to a poor rehabilitation prognosis (15–17). In addition, stroke patients often have lower motor motivation, which may lead to a lack of rehabilitation motivation and hinder functional recovery (18). When patients have a high level of rehabilitation motivation, their participation also increases, which is beneficial for improving their activities of daily living (19). Therefore, it is necessary to add auxiliary intervention to alleviate the negative emotions of patients with upper limb dysfunction after stroke, so as to urge them to actively cope with functional rehabilitation treatment and finally improve rehabilitation outcomes.

Indicated to be physically and mentally helpful, reminiscence therapy has been gradually applied to improve the cognitive function and mental health of older patients with stroke (20–22). Music is one of the most common media to trigger nostalgia, which can not only have a positive effect on patients by evoking nostalgia but also treat physical or psychological diseases by musical sound and rhythm (23). A theoretical model suggested that music, when combined with nostalgia, can help summon autobiographical memories, evoke strong emotions, elicit physiological responses to improve physical wellbeing and immunity, and develop self-definition (24). Moreover, a previous study believed that adding music elements may increase the intrinsic motivation of patients in the process of rehabilitation treatment (25). Music activates both the auditory system and sensory-motor system simultaneously, and helps to reorganize and integrate information processing, executive control, and emotions, so as to shift attention away from fatigue and promote the acquisition of motor skills (26, 27). These literature provide a theoretical basis for the combination of reminiscent music therapy with robot-assisted rehabilitation. In accordance with these studies (20–22), it is suggested that the definition of reminiscent music therapy is a combination of music therapy and reminiscent therapy, meaning that using music can prompt and augment the recollection of autobiographical memories and help people think about the meaning of life and experiences, which helps to alleviate negative emotions and improve positive attitudes and hope levels.

Therefore, the aim of this study is to evaluate the efficacy of reminiscent music therapy combined with robot-assisted rehabilitation in improving the physical and mental health and promoting the self-care abilities of older stroke patients with upper limb dysfunction by conducting a randomized controlled trial. The hypothesis is that reminiscent music therapy combined with robot-assisted rehabilitation plus usual care may be more effective than robot-assisted rehabilitation plus usual care or only usual care with respect to improving activities of daily living and other outcomes.

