#### Statistical methods

2.7.1

We will use IBM SPSS Statistics 22 to analyze the data, and all tests are two-sided. Statistical significance is defined as a *p*-value of <0.05. Confidence intervals (CIs) will be stated at the 95 confidence level. A P–P diagram will be used to test the normal distribution of measurement data. The statistical description of measurement data will use the mean and standard deviation when following a normal distribution; otherwise, use the median and quartile. When following normal distribution and homogeneity of variance, the measurement data will be compared by the analysis of variance for intergroup comparison, a paired-sample t-test will be used for intragroup comparison, and a multifactorial analysis of variance will be used to evaluate the interaction effects. Otherwise, the Kruskal–Wallis H-test will be adopted for intergroup comparison, and the Wilcoxon signed rank sum test will be used for intragroup comparison. Counting data will be described by number and percentage. The chi-square test and Fisher’s exact test will be used to analyze the counting data. If the baseline indicators are not comparable, an adjustment to the efficacy contrast of variables such as age, sex, and diagnosis is required. In patients where baseline indicators are unbalanced, an adjustment to the efficacy contrast of variables such as age, sex, and concurrent therapy is required. The covariance approach will be used for continuous variables, and logistic regression analysis will be used for counting data.

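### The tests fixed in section 2.7.1 do not isolate music plus robot versus robot, the only comparison that shows what the music adds

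*Protocol article*

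**What the plan says.** Section 1 (Introduction) states the hypothesis that the combined arm "may be more effective than robot-assisted rehabilitation plus usual care or only usual care" for activities of daily living and other outcomes. It involves two comparisons, and experimental group 1 is in both: group 1 versus group 2, and group 1 versus control.

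Section 2.7.1 (Statistical methods) fixes the following for continuous outcomes:

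- Between arms: "the measurement data will be compared by the analysis of variance for intergroup comparison". If the normality or equal-variance conditions fail, "the Kruskal–Wallis H-test will be adopted for intergroup comparison".
- Within arms: "a paired-sample t-test will be used for intragroup comparison", or the Wilcoxon signed-rank test.
- Interaction: "a multifactorial analysis of variance will be used to evaluate the interaction effects". The factors are not named.
- Level: p<0.05, and "all tests are two-sided".
- Covariates, if baseline is not comparable: "an adjustment to the efficacy contrast of variables such as age, sex, and diagnosis is required". The arms in this contrast are not defined.

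Sections 2.3 and 2.5 give three arms in a 1:1:1 ratio: control, music plus robot, and robot. No arm receives music without the robot. Section 2.1 sets a floor of 35 per group and leaves the final number until after a pilot. Section 2.6 makes activities of daily living at T1 the primary outcome, and section 2.6.6 measures it with the modified Barthel Index.

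**The concern.** What is new in this trial is the addition of reminiscent music to robot training. The Discussion also expects the robot to improve on usual rehabilitation without music. So a result in which the robot works and the music adds nothing is a realistic one, and the analysis has to tell it apart from a music effect.

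The tests named in section 2.7.1 do not do so. A significant three-group test says that some arms differ, not which. Within-arm tests mix treatment with natural recovery, and section 2.2 admits acute and subacute patients. An investigator who followed the section as written could have a significant between-group result, and significant improvement within the music arm, with no evidence that music helped.

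**Working it through.** **1. Match each named test to the hypothesis**

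| Test in section 2.7.1 | Question it answers | Isolates group 1 vs group 2? |
|---|---|---|
| Three-group ANOVA or Kruskal–Wallis | Do any of the three arms differ? (2 df) | No |
| Paired t-test or Wilcoxon | Did this arm change from T0 to T1? | No |
| Interaction, if music by robot | Does the effect of music depend on the robot? | Not estimable: the music-without-robot cell is empty |
| Interaction, if group by time | Do any arms differ in change? (2 df) | No: another omnibus test |

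**2. How often the omnibus test rejects when music adds nothing**

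Inputs:

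- n = 35 per arm, the floor in section 2.1.
- Two-sided alpha 0.05, from section 2.7.1.
- Standardised means of 0 (control), d (robot) and d (music plus robot), so the music effect is 0.
- The robot effect d is an assumption, since the article gives no effect or SD for the modified Barthel Index. A range is shown.

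The mean of the three means is 2d/3, so the sum of squared deviations is (4/9 + 1/9 + 1/9)d² = (2/3)d². The noncentrality is λ = n × (2/3)d² = 23.33d². The degrees of freedom are 2 and 3(35 − 1) = 102, and the critical F is 3.085. The rejection probability is the upper tail of the noncentral F beyond that value.

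| Assumed robot effect d (SD) | λ | P(omnibus F significant), music effect 0 |
|---|---|---|
| 0.2 | 0.93 | 12% |
| 0.3 | 2.10 | 23% |
| 0.5 | 5.83 | 56% |
| 0.7 | 11.43 | 86% |
| 0.8 | 14.93 | 94% |

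With 30 per arm (35 less about 15% loss) the figures are 11%, 20%, 49%, 79% and 89%. A final number above 35 raises them.

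**3. Do the alternatives in the section repair this?**

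By simulation at 35 per arm, still with zero music effect, Kruskal–Wallis rejects in 55% of trials at d = 0.5 and 92% at d = 0.8. A group-by-time test, with an assumed T0–T1 correlation of 0.6, rejects in 66% and 98%. Both respond to the robot alone, as the F test does.

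**4. With the contrast named**

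A test of group 1 versus group 2 at two-sided 0.05 rejects in 5% of trials when music adds nothing (2.5% in favour of music), whatever the robot effect. Its power at 35 per arm for an assumed music effect of 0.5 SD, by the normal approximation, is Φ(0.5 × √(35/2) − 1.96) = Φ(2.09 − 1.96) = 55%. For 80% power at 0.5 SD, n = 2(1.96 + 0.84)²/0.5² = 62.8, or 63 per arm before dropout.

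**The case against.** The strongest reply is that this is an article. Post-hoc comparisons, testing order and multiplicity rules are commonly left to a fuller plan, an ANOVA model can supply any pairwise contrast, and the phrase about an efficacy contrast suggests that contrasts are intended. Nor does any section say that a significant omnibus F makes the trial positive. All of this stands. The absence of post-hoc tests is not the point. The point is that the tests that are written do not match the hypothesis that is written, and the one contrast mentioned has no arms attached.

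The effect sizes also have no source in the article. Its claims for the robot concern mainly muscle coordination, upper limb function and social participation rather than the Barthel score. The range therefore has to include small effects, where the problem is milder (12% at 0.2 SD).

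Three stronger readings are tempting, and the documents do not support them:

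- **The word joining the two comparators lets a win over either count.** The wording is ambiguous. Better than one or the other can equally mean better than both, and no success rule is stated.
- **False-positive error exceeds 5%.** The hypothesis is directional. With no true effects, group 1 is significantly better than at least one comparator in about 4.5% of trials, even with ungated pairwise tests at 0.05. No section proposes ungated tests. If pairwise tests follow a significant F, the error over all three pairs is about 5%.
- **The interaction ANOVA treats T0 and T1 as independent.** The model is not specified, so this is a guess. It would also inflate standard errors and make the test conservative.

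**Conclusion.** The point holds as a mismatch between hypothesis and analysis. Followed as written, section 2.7.1 gives no test that can support the claim that music adds to robot training. An omnibus result can be significant in 12% to 94% of trials with a zero music effect, over assumed robot effects of 0.2 to 0.8 SD at 35 per arm. Those percentages rest on the assumed effects, on normal outcomes with equal variances, and on the section 2.1 floor being the analysed number. The direction does not depend on them: any real robot effect lifts the omnibus rejection rate above 5% when music does nothing. The documents do not establish that the trial would be declared positive on the omnibus test, or that its type I error is inflated.

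**What to change.** **Section 1.** Reword the hypothesis so that it states both contrasts separately: group 1 is more effective than group 2, and group 1 is more effective than control.

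**Section 2.7.1.**

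- Name group 1 versus group 2 on the modified Barthel Index at T1 as the contrast on which any claim about music rests, tested first at two-sided 0.05.
- If it is significant, test group 1 versus control at two-sided 0.05 (fixed sequence).
- Make group 2 versus control secondary.
- Report each difference with its 95% confidence interval.
- State that efficacy claims will not rest on the omnibus, interaction or within-arm tests.
- Say which arms the efficacy contrast in the covariate sentences compares.

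**Cost.** The text change is short and needs no new data. There are two small downsides. A win over usual care cannot be claimed if group 1 versus group 2 fails. At the floor of 35 per arm the music contrast has only about 55% power for an assumed 0.5 SD, so a null result there would be weak evidence. Whether to enrol more is a separate decision, to be weighed when the sample size is calculated after the pilot. This change does not require it, and it leaves the existing rule on covariate adjustment as it is.

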## Methods

2

This study is a single-blind, three-arm randomized controlled trial with randomization at the participant level. This trial was approved by the Ethics Committee of West China Hospital of Sichuan University (number: 2022–852) and was registered on the Chinese Clinical Trial Registry (number: ChiCTR2200063738). Activities of daily living will be the primary endpoint to examine whether usual rehabilitation treatment and care plus robot-assisted rehabilitation and reminiscent music therapy for older patients with upper limb dysfunction after stroke improve physical and mental health. All outcomes will be collected for three groups at baseline (T0) and in the week immediately post-intervention (T1). The overview of the study design is shown in Figure 1, and this study protocol followed the statement of the Consolidated Standard of Reporting Trials (CONSORT) (28).

**Figure 1 fig1:**
[figure not shown]
CONSORT flow diagram of this study.

### Study setting

2.1

This trial will be conducted at the West China Hospital of Sichuan University in Chengdu, China. Stroke patients aged 60 years and older with upper limb dysfunction who are hospitalized in the Department of Neurology of this hospital will be recruited. The department is a national key clinical specialized department, which ensures that enough participants can be recruited for this trial. It is estimated that 10 stroke patients aged 60 and above can be accommodated per month, who are expected to be hospitalized for up to 20 days and can accept rehabilitation training for 3 weeks. Therefore, in accordance with the availability of the patients and a loss of follow-up rate of 10 to 15%, we plan to recruit 12 stroke patients aged 60 and above first to conduct a pilot study. The sample size will be calculated using PASS software based on the scores of activities of daily living after the pilot study. Each group will have no less than 35 people.

### Recruitment

2.2

Participants will be recruited from the Department of Neurology at West China Hospital of Sichuan University. Researchers will recruit participants by approaching potentially eligible participants in the neurology ward. Inclusion criteria of participants are (1) newly admitted patients diagnosed as stroke, including ischemic or hemorrhagic strokes for the first time, (2) 60 years old and above, (3) conscious and in stable condition with stable vital signs, whether in the acute, subacute, or chronic phase of stroke, (4) with upper limb dysfunction and Brunnstrom stages I to VI, (5) normal cognitive function without minimal aphasia or hemineglect, (6) normal vision, hearing, and communication, (7) no music-related learning experience and acceptance of music, and (8) participating in this study voluntarily and signing the informed consent form. Exclusion criteria are (1) severe primary diseases of the heart, liver, kidney, and hematopoietic system, (2) a history of mental disease, (3) joint dislocation or skin damage of the upper limb, (4) largest slice diameter of cerebral infarction is greater than 3.0 cm, or the infarction spreads to two brain lobes, or the volume of intracerebral hematoma is greater than 30 mL, (5) uncooperative participants, (6) depression according to the Self-rating Depression Scale. After determining the eligibility of interested patients, the researchers will describe the details of this study to them again, obtain written consent forms, and collect baseline data.

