### Randomization

2.3

The random number table was generated based on the RV.Uniform function of SPSS 22.0 software. All participants will be randomly assigned to one of the three groups in a 1:1:1 ratio after initial evaluation. Participants will be randomly allocated via an online service provided by the Innovation Center of Nursing Research at the West China Hospital.

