#### Robot-assisted rehabilitation

2.5.2

According to the specific conditions of the patients, the rehabilitation doctors will use the rehabilitation robot for the upper limb to carry out 40 min of rehabilitation training for the patients, five times per week for 3 weeks. The individualized rehabilitation scheme will be formulated by rehabilitation doctors and neurologists according to the specific situation of the patients. The robot equipment used in this study is a three-dimensional upper limb rehabilitation robot (model: A6) produced by Guangzhou Yikang Medical Equipment Industry Co., Ltd. Rehabilitation doctors need to undergo strict training from the manufacturer before they can operate the equipment. This robot equipment has five training modes: passive mode, active-passive mode, active mode, prescription mode, and track editing mode.

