### Outcomes and measurements

2.6

A research assistant who does not know the randomization scheme will perform the data collection and examinations at baseline (T0) and in the week immediately post-intervention (T1). Every time to measure data is face-to-face with participants. We expect the intervention to improve the abilities of patients to take care of themselves. Therefore, we choose the activities of daily living measured in the week immediately post-intervention (T1) as the primary outcome. Self-esteem, rehabilitation self-efficacy, positive emotion, upper limb function, and safety will be the secondary outcomes.

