#### Demographic data (T0)

2.6.1

To characterize the participants, the sex, age, educational level, marital status, residence, nationality, religion, monthly income *per capita* of family, type of medical insurance, diagnosis, phase of stroke, type of combined chronic disease, Brunnstrom stage, and main caregivers will be collected.

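### Every phase of stroke is eligible and phase is recorded, but the primary Barthel comparison adjusts for it, if at all, only after observed imbalance; the first-time wording also needs clarifying

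*Protocol article*

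**What the plan says.** **Eligibility (protocol article, 2.2 Recruitment).** Criterion (1) asks for "newly admitted patients diagnosed as stroke, including ischemic or hemorrhagic strokes for the first time". Criterion (3) asks for patients who are "conscious and in stable condition with stable vital signs, whether in the acute, subacute, or chronic phase of stroke". Criterion (4) takes those "with upper limb dysfunction and Brunnstrom stages I to VI". No inclusion or exclusion criterion limits the time from onset to enrolment.

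**Baseline data (2.6.1).** The list ends with "diagnosis, phase of stroke, type of combined chronic disease, Brunnstrom stage, and main caregivers will be collected", so phase is known for every participant.

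**Allocation (2.3).** Participants are "randomly assigned to one of the three groups in a 1:1:1 ratio after initial evaluation". Stratification by phase is not mentioned.

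**Primary outcome (2.6, 2.6.6).** The authors write that "we choose the activities of daily living measured in the week immediately post-intervention (T1) as the primary outcome". It is scored with the modified Barthel Index, 0 to 100. Robot training runs "five times per week for 3 weeks" (2.5.2).

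**Analysis (2.7.1).** Groups are compared by analysis of variance, or by the Kruskal–Wallis test if its assumptions fail. Covariance adjustment is reserved for the case where baseline is found not comparable. Two sentences give example covariates: age, sex and diagnosis in one; age, sex and concurrent therapy in the other. Phase appears in neither. A multifactorial analysis of variance is mentioned for interaction effects, without naming its factors.

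**The concern.** The article opens entry to every phase of stroke and records phase, but gives phase no planned part in the primary comparison. Over a three-week course, the Barthel score afterwards may plausibly depend on how long ago the stroke happened, quite apart from treatment. If it does, an unadjusted comparison counts that difference as noise although the variable that explains it is already in the data set. Adjusting only after an imbalance has been seen does not solve this: a prognostic covariate improves precision even when the arms are balanced on it, and a rule triggered by the observed data leaves the primary model open until the baseline table is known.

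The second matter is wording. In criterion (1), the clause about a first occurrence is attached by the word including. It can mean that only first-ever strokes qualify, that the stroke must be newly diagnosed at this admission, or merely that first strokes are among those accepted. A recruiter facing a patient admitted now, whose only stroke was a year ago, would include that patient on the first reading and exclude the same patient on the second.

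**Working it through.** **1. Can criteria (1) and (3) both be met?** Yes. Criterion (1) refers to admission to the ward and criterion (3) to the phase of the stroke. A patient whose first stroke was months ago and who is admitted now satisfies both. The fault is unclear wording.

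**2. The plan's own figure.** Section 2.1 sets a floor of 35 per group and defers the calculation until after a pilot. It states no effect size, SD or power, so 35 cannot be reproduced. For orientation only, assume 80% power, two-sided 0.05 (the level in 2.7.1) and one pairwise comparison:

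d = (1.960 + 0.842) × √(2/35) = 2.802 × 0.239 = 0.67 within-phase SD.

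**3. Effect of leaving phase out of the model.** Let q be the chronic share and g the gap between chronic and earlier-phase patients in mean post-intervention Barthel, in within-phase SDs. Both are assumptions, and the three phases are collapsed to two for simplicity.

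- SD inflation = √(1 + q(1 − q)g²)
- Power = Φ(0.67 × √(35/2) / inflation − 1.960)

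Worked example, q = 0.05 and g = 1: inflation = √(1 + 0.0475) = 1.023. The first term is 0.67 × 4.183 / 1.023 = 2.74. Power = Φ(0.78) = 78.2%.

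| q (chronic) | g (SD) | SD inflation | Power at 35 per arm | n per arm for 80% |
|---|---|---|---|---|
| any | 0 | 1.000 | 80.0% | 35 |
| 5% | 1.0 | 1.023 | 78.2% | 37 |
| 20% | 0.5 | 1.020 | 78.5% | 37 |
| 50% | 0.5 | 1.031 | 77.6% | 38 |
| 20% | 1.0 | 1.077 | 74.0% | 41 |
| 30% | 1.0 | 1.100 | 72.2% | 43 |
| 50% | 1.0 | 1.118 | 70.8% | 44 |

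A gap of 1.5 SD would cost more (67.1% power at 20% chronic, 61.1% at 50%), but nothing in the article points to a gap of that size.

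**4. What adjustment recovers.** In this model the phase label explains all of the added variance, so including phase brings the inflation back to 1. Days since onset would add something only if outcome also varies with time within a phase, which this model does not represent.

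**5. A limit of the model.** The primary outcome is the score after the intervention, not the change. The gap g equals the difference in recovery only if the phases start from equal mean Barthel scores. If early patients start lower and gain more, g is smaller than the recovery difference and the loss is smaller too.

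**The case against.** **The criteria contradict each other.** A reader might infer this from setting a new admission beside a chronic phase. The text does not support it, as step 1 shows. Criterion (3) names all three phases and reads as a deliberate choice of a broad population.

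**Chronic patients should be excluded.** A reader might also infer that the mixture makes the result invalid or applicable to nobody. Random allocation keeps the group comparison unbiased, and the population can be described: older neurology inpatients with stroke, with phase recorded. A broad population is legitimate, and reasonable trialists differ on it.

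**The loss may be small.** This stands. Chronic patients may be few on an acute neurology ward, and at a 5% share even a 1 SD gap costs only about 2 points. The larger losses need a sizeable chronic share as well, and the article supplies neither the share nor the gap.

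**The pilot will absorb the mix.** Section 2.1 calculates the sample size after a 12-patient pilot, whose SD would reflect whoever is enrolled. This is partly right, and it means there is no stated design power to erode. But 12 patients fix the mix poorly: at an assumed 20% chronic share, the chance of none or one chronic patient is 0.8¹² + 12 × 0.2 × 0.8¹¹ = 0.069 + 0.206, about 27%. An SD that carries the phase variance also asks for more patients than an adjusted analysis needs.

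**Adjustment for phase is already allowed.** The covariate lists in 2.7.1 are examples, so phase could be added. It remains conditional on imbalance and is not named. The full protocol or analysis plan, not shown, may say more, and numeric phase limits or an onset-date field may properly be left there. The conditional rule, however, is what this article states.

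**Conclusion.** The point holds as one of precision and clarity. A population that openly spans all phases is compared without adjustment for a recorded variable that plausibly predicts the outcome, and the stated rule brings in covariates only after an imbalance is seen. On the assumptions above (80% power at 35 per arm, two-sided 0.05, two phase groups, equal within-phase SD), the cost runs from about 2 points of power (0.5 SD gap, or 5% chronic with a 1 SD gap) to 6 to 9 points (1 SD gap, 20% to 50% chronic). In the latter case, 41 to 44 per arm would be needed in place of 35. These are illustrations, since the documents give no case mix and no recovery by phase. They show neither bias nor a contradiction between the criteria. The first-time clause in criterion (1) is ambiguous and should be settled.

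**What to change.** - **Section 2.7.1:** make the primary comparison of post-intervention Barthel scores an analysis of covariance with stroke phase as a prespecified covariate, whatever balance is observed. Days since onset, taken from the hospital record, could be used in its place.
- **Section 2.2:** say whether the first-time clause in criterion (1) means first-ever stroke, and word criteria (1) and (3) so that they read together. Whether chronic-phase patients remain eligible is for the sponsor to decide; the analysis change is useful either way.

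**Cost:** a few sentences of wording and one or two degrees of freedom (two for a three-level phase factor, one for a linear term in days). Phase is already collected; days since onset would need one extra date field.
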